### Exclusion criteria

CHPS zones that are not a certified National Health Insurance Scheme provider will be excluded.

Patients will be excluded if they meet the following g criteria: (a) those with previous diagnosis of diabetes, stroke, heart failure, or chronic kidney disease; (b) BP > 180/100 mmHg; (c) positive urine dipstick for protein; (d) pregnancy; and (e) inability to provide informed consent. Patients with history of stroke, heart failure, diabetes, angina, claudication, and BP > 180/100 mmHg will be referred to the district hospitals.

### Ethical approval and trial protocol

Ethical approval for this study was obtained from the Kintampo Health Research Centre Institutional Ethics Committee; Kwame Nkrumah University of Science and Technology Committee on Human Research, Publication, and Ethics; and the Ghana Health Service Ethics Review Committee.

### Randomization and blinding

Randomization will occur at the level of the CHPS zones. Each CHPS zone will be randomly assigned to one of the two arms: Group A will receive the practice facilitation strategy herein referred to as a task-strengthening facilitation (TSF) strategy for 12 months. Assessment of adoption ratings on TASSH will be made at 12 months post-randomization, and sustainability will be assessed at 24 months post-randomization. Group B will receive usual care practices (screen, counsel, and refer patients without practice facilitation) at CHPS zones [27]. Adoption ratings of TASSH will be assessed for group B at 12 months post-randomization, and sustainability assessment will occur at 24 months post-randomization. The sequence of randomization will be generated by study statistician and kept in sealed opaque envelopes away from the study sites in accordance with the CONSORT guidelines [29]. Sites will be informed of their randomization group by telephone and email.

#### Masking and blinding

Due to the nature of the intervention, it is impossible to blind the patients, the community health officers, and the study coordinators to the group assignment of each intervention. However, the salient dimension that the study coordinator could possibly affect is the BP measurements. To mitigate this bias, we will use an automated BP device, which prevents the study coordinator from influencing in any manner the BP readings. We anticipate that this trial will not pose any direct harm to the participants as no treatment/medication/supplement will be administered by the trial to participants. Participants will be referred to the nearest district hospital for treatment of any conditions they may develop during the period of this trial. Enrolling in this trial will not prohibit study participants from accessing medical care for any condition they may have.

The trial flow chart is shown in Fig. 1, and the SPIRIT figure is shown in Fig. 2. The SPIRIT checklist is provided in Additional file 1. As shown in Fig. 1, all CHPS zones enrolled will be randomly assigned to either group A, the intervention group (*N* = 35), or group B, the control group (*N* = 35). A total of 70 CHPS compounds and 700 patients will be enrolled in this study with approximately 10 patients per CHPS compound. We considered randomizing patients, but the likelihood of contamination represents a threat to internal validity; thus, patients will be nested within the CHPS compounds. CHPS zones randomized to group A will receive the task-strengthening facilitation (TSF) intervention, as described in the “Intervention conditions” section below. Group B will receive health information based on the TASSH protocol. The only difference is that CHPS zones in the usual care group will not receive practice facilitation. Approximately two CHOs will be trained per CHPS compound, providing a sample of 140 CHOs overall and 70 CHOs per condition. Also shown in Fig. 1 is the facilitation schedule which will occur at months 3, 6, and 9 of the intervention periods and the assessment points in each group.

**Fig. 1 Fig1:**
[figure not shown]
Trial implementation design (parallel)

**Fig. 2 Fig2:**
[figure not shown]
TASSH SPIRIT figure

### Intervention conditions

Participants will be assigned to either the practice facilitation group (group A) or the usual care group (group B).

#### Practice facilitation (group A)

Patients belonging to the intervention group will go through the same process as those of the usual care group. The CHOs in this group will receive the task-strengthening facilitation delivered by the task-strengthening facilitators. The practice facilitation intervention (intervention group) has three components:
i.Training of TSFs on *Engaging*, *Enhancing*, and *Evaluating* their tasks at the CHPS zones. The TSFs will carry out this function via onsite and remote supportive supervision of the CHOs. The basis of the strategy is to *Engage* the CHOs (via monthly phone calls to address barriers that the CHOs may have in performing their duties) and *Enhance* the CHOs (via onsite visits quarterly to observe and supervise them in their duties) and use of learning communities. Study staff will certify and re-certify the TSFs as trainers yearly using a train-the-trainer model. This will be accomplished via a training module consisting of the following: (1) Training on BP measurement and how to identify, screen and refer patients to the health centers for treatment. (2) Training on counseling strategies for engaging CHOs, enhancing them, and evaluating their tasks. The TSFs will be trained to map out the list of tasks that the CHOs will perform, categorize the list of tasks into three groups (screening for diagnosis of HTN, counseling, and referral), and create scenarios and examples of how to use the EEEs around each task. The scenarios will be in Twi language and at elementary school level. (3) Training on use of the online learning communities such as WhatsApp to engage the CHOs. (4) Training on use of remote phone calls and onsite supervision of the CHOs. The TSFs will be trained by study staff to communicate with the CHOs remotely via telephone calls and via onsite visits. The phone calls will occur once a week for at least an hour in duration, while the onsite visits will occur every 4 months for duration of 1 day. CHOs will be trained to develop a list of participants contacted, counseled, and referred using an electronic monitoring system. They will be trained to develop a checklist for the phone calls and another for the site visits.ii.Training the CHOs on identifying, counseling, and referring (ICR) of adults with HTN to the health centers using the 5 A’s counseling strategy (Ask, Assess, Advise, Assist, and Arrange) [30]. Similarly, study staff will create a training module for the CHOs. Components of the module are as follows: training on BP measurement and training on how to identify, counsel, and refer patients with HTN to the community health centers for treatment. This counseling strategy will use the 5 A’s (Ask, Assess, Advise, Assist, and Arrange) [30]. Duration of the training of the CHOs and TSFs will be three full days. The initial training will be supplemented by booster trainings of the same duration every 3 months in order to minimize drift. In order to guarantee sustainability, study staff in Ghana will be trained to deliver this training to CHOs every 6 monthsiii.Creation of a community learning environment to support learning opportunities for the CHOs and TSFs. Study staff will develop information that will be shared on the WhatsApp group with the CHOs and TSFs. Study staff will create a series of messages that will be sent via WhatsApp as a structured blast to CHOs and TSFs. Every 2 weeks, a short message about a topic on HTN will go out to both groups. Similarly, there will be an *Ask the Expert Forum*. These messages will include information on BP measurement techniques, counseling skills, and sharing of hypertension education material. Other information will include tips on identification, counseling, and referral of patients to health centers.

##### Engagement of the community to create a community urgency and persistency of the importance of HTN screening and referral for adults

This component of the intervention will be conducted by the Local Steering Committee that comprises the leadership of the regional health directorate, public health nurses, director of surveillance, coordinator for the community engagement committee, data manager, and the regional NCD resource person. This committee is already convened as part of the Ghana Health Services and will coordinate the community engagement activities via health fairs, visits to health centers, and other events organized by the Regional Health Directorate of the Brong-Ahafo Region where the participating CHPS zones are located.

#### Usual care (group B)

CHOs based at group B facilities will be trained on the 5 A’s and referral of the participants to the health center. However, they will not receive practice facilitation from the TSFs. Participants attending CHPS zones randomized to group B will receive standard care offered by that CHPS facility.

### Study outcomes

*Primary outcome* is the rate of adoption of TASSH at the CHPS zones at 12 months. This will be based on a composite measure of three adoption ratings (i.e., number of newly detected hypertensive patients identified by the CHOs, proportion of patients receiving lifestyle counseling, and referred for further management by the CHOs). The primary outcome will be assessed at 12 months post-randomization by the following measures:
*Rate of newly detected hypertensive patients*: Of the number screened by the CHOs, how many were identified as hypertensive (BP > 140/90 mmHg)?*Proportion of patients receiving lifestyle counseling*: Of the number identified by each CHO as hypertensive, how many received lifestyle counseling?*Proportion of eligible patients that were referred to community health centers for further management*: Of the number identified by each CHO as hypertensive, how many were referred to the community health center for further management? In order to assess these measures, the CHOs will complete a questionnaire inquiring about newly diagnosed hypertension and behavioral counseling practices; the retention and referral rates for patient follow-up at each study visit will be monitored. CHOs who have increased rates for all three metrics will be identified as having adopted the TASSH intervention.

*Secondary outcomes* are as follows:
Mean reduction in patient systolic blood pressure (BP) at 12 months post-randomization.Mediators (implementation climate, leadership support, organizational capacity, and provider-level characteristics) of the adoption of TASSH across the CHPS zones at 12 and 24 months will be assessed.Rate of adoption of TASSH at the participating CHPS zones at 24 months post-randomization (sustainability).

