### Study setting and participant characteristics

The study is currently ongoing in 70 of the 97 CHPS zones in three contiguous districts within the Bono East Region (Kintampo North, Kintampo South District, and Nkoranza North District) of Ghana. The study area is predominantly rural and mostly farming communities [26, 27]. About 40% of the adult population have no education. Access to healthcare is mainly at the community-level healthcare which is limited. About 50% of the population have valid health insurance cards that enable them to access basic healthcare under the National Health Insurance Scheme. In 2016, 2555 community members aged ≥ 18 years (mean age of 43 years, SD 17; 60.5% female) participated in a cross-sectional health survey, which documents the prevalence of hypertension as 28.1% (95% CI 26.3–29.8), with pre-hypertension prevalence of 42.5% [28]. Approximately 45.9% (95% CI 42.2–49.6) of hypertensive respondents were aware of their diagnosis; of those aware, 41.3 (95% CI 36.1–46.8) sought medical treatment and had their hypertension controlled, while 58.7% (95% CI 53.2–63.9) did not seek any medical treatment. Tobacco use in the area is about 3%, and the prevalence rate of obesity among the adult population (> 40 years) is 11% [28].

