
#### Analysis for aim 2a: The adoption of TASSH will be higher in the CHPS compounds randomized to the PF strategy than those in usual care at 12 months post-randomization

This analysis will be accomplished with a multilevel mixed model using an unstructured covariance matrix across two time points, baseline and 12 months. The analysis will have one within-person factor—time (baseline and 12 months coded naturally as months 0 and 12)—and one primary between-patient factor (randomization group dummy coded as 0 = UC and 1 = PF). Fixed effects will be specified for time, randomization group, and their interaction effect (group by time). The outcome measure will be a composite index for adoption of TASSH (defined as rate of identification of HTN, rate of lifestyle counseling for patients with HTN, and medication referral for patients with HTN). Additionally, the CHOs will be nested within compounds creating a 3-level analytic model (observations nested within CHOs nested within compounds). Random effects will be specified for CHPS and for CHO, adjusting for the clustering of measures within CHO and CHO within CHPS. Multilevel modeling software (SAS, version 9, PROC MIXED) will be used to compute full information maximum likelihood (FIML) estimates of the model parameters. The PROC MIXED procedure will use an error structure that allows for the possibility of group differences in (a) the error variances at 12 months and (b) the serial correlations of the baseline with the 12-month outcomes. The primary test is the group × time interaction, and the resulting *F* test will provide the primary “intent to treat” test of the hypothesis. If this is statistically significant at the two-tailed *α* = .05 level, for ease of interpretation, we will estimate and report the magnitude of the treatment effect, with 95% CI for adoption. Ideally, the randomization of participants to treatment groups will obviate the need for any covariates in the analysis. However, in the event that baseline differences between the patients in each group on the outcomes, demographic, or secondary measures are found, those variables will be included as covariates in the model (including their interactions with time).

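### The detection component of the primary outcome is defined both as a count and as a share of those screened, and the share gives a CHO no credit for screening more people

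*Protocol article*

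**What the plan says.** The primary outcome is a composite of three adoption measures at 12 months. Study outcomes introduces the first of them as the "number of newly detected hypertensive patients identified by the CHOs", which is a count. The itemised definition that follows labels it a rate and asks: "Of the number screened by the CHOs, how many were identified as hypertensive". That is a proportion whose denominator is the number the CHO screened.

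The same section gives a classification rule: "CHOs who have increased rates for all three metrics will be identified as having adopted the TASSH intervention".

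The aim 2a analysis models a composite index "defined as rate of identification of HTN, rate of lifestyle counseling for patients with HTN, and medication referral for patients with HTN". It does not say what the identification rate is divided by.

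Screening is one of the tasks the strategy supports. Under Practice facilitation (group A), facilitators are trained to list the CHOs' tasks and "categorize the list of tasks into three groups (screening for diagnosis of HTN, counseling, and referral". A community engagement component under the same section aims to "create a community urgency and persistency of the importance of HTN screening and referral for adults".

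**The concern.** A count of new cases rises when a CHO screens more people. The share positive among those screened does not. It depends on who is screened, and the number screened enters it only as the denominator. One third of the primary composite therefore has two definitions that can rank the same CHO differently.

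Three things follow if the share is used as written:

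- A CHO who extends screening at an unchanged yield finds more hypertensives but has no expected increase on this component. Whether the observed rate goes up, and so whether the CHO can count as an adopter, is then left to chance.
- If the added people have a lower yield than those screened before, the score falls while detection rises.
- A CHO can raise the share by measuring fewer, higher-risk people. Masking and blinding says CHOs know their allocation, and Study outcomes has them supply the data by questionnaire.

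At stake are the adopter classification and, through the index, the group-by-time test for the primary outcome.

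**Working it through.** **1. The plan's own figure.** Inputs from Sample size and power estimates: d = 0.50, ICC = 0.10, 2 CHOs per compound, power 0.80, alpha 0.05 (two-sided, from the aim 2a analysis).

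- Per arm without clustering: 2 × (1.960 + 0.842)² / 0.50² = 62.8, so 63.
- Design effect: 1 + (2 − 1) × 0.10 = 1.10, and 63 × 1.10 = 69.3 CHOs per arm.
- Compounds: 69.3 / 2 = 34.65, so 35 per arm and 70 in total.

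The stated 70 compounds and 140 CHOs reproduce. The sample-size arithmetic is not in question.

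**2. Direction of the share.** Let a CHO screen N0 people at yield y0, then widen to N1 people, with the added people having yield p.

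- Cases after = N0·y0 + (N1 − N0)·p
- Share after = cases after / N1
- Change in share = (N1 − N0)(p − y0) / N1

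The count always rises. The share falls if p < y0, is unchanged if p = y0, and rises if p > y0.

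**3. Numbers.** Study setting and participant characteristics gives "the prevalence of hypertension as 28.1"% of adults aged 18 or over, with 45.9% of hypertensive respondents aware of their diagnosis. The component concerns new detections, so p = 0.281 × (1 − 0.459) = 0.152. N0 = 50, N1 = 150 and every y0 are assumptions; the article gives none of them.

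| Starting yield y0 (assumed) | New cases before | New cases after | Share after |
|---|---|---|---|
| 40% | 20.0 | 35.2 | 23.5% |
| 30% | 15.0 | 30.2 | 20.1% |
| 15.2% | 7.6 | 22.8 | 15.2% |
| 10% | 5.0 | 20.2 | 13.5% |

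The count rises 1.8-fold (35.2 / 20.0) to 4.0-fold (20.2 / 5.0). The share falls in two rows, is flat in one and rises in one.

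**4. Sensitivity to counting known cases.** If everyone with a raised reading counts, p = 0.281. From 50% the share falls to 35.4% (25 to 53.1 cases). From 40% it falls to 32.1% (20 to 48.1). At 28.1% it is flat (14.05 to 42.2). From 20% it rises to 25.4% (10 to 38.1). The pattern is the same.

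**5. The reverse case.** Read the 30% row backwards. A CHO who cuts screening from 150 people to the 50 with the higher yield moves the share from 20.1% up to 30% while new cases fall from 30.2 to 15.

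**The case against.** The strongest reply is that the conflict is only one of wording. The itemised label says rate, its definition names a denominator, the adopter rule speaks of rates, and so does the aim 2a analysis. Only the introductory list uses a number. On that reading the share governs. This has force, but it settles the matter in favour of the form that ignores screening volume, and the aim 2a text still leaves the denominator open.

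A reader might infer that a CHO who widens screening necessarily scores lower. The documents do not support that. A fall needs the added people to have a lower yield than those screened before, and no baseline yield, screening volume or pre-selection of at-risk people is reported. Sites and participant recruitment describes contact during routine services, family visits and health fairs, which is not plainly a high-risk pool.

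A reader might also infer that the primary comparison is biased against facilitation. That is not shown either. Health fairs are described for participating zones generally, not for group A alone. The engagement activities work through an existing regional committee, and no target for numbers screened is set. The primary test uses a composite index whose construction the article does not give, and the counseling and referral components do not use the number screened as denominator. That the strategy intends wider screening is a fair inference from its task list and engagement component, not a stated aim.

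The manual of operations mentioned under Trial status may say who is to be screened. That could narrow the range of yields but would not reconcile the two definitions.

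**Conclusion.** The point holds in a conditional form. The article gives one component of its primary outcome two incompatible definitions, and the more detailed one gives no credit for detecting more cases by screening more people. Showing no expected gain needs only an unchanged yield. A falling score needs the further assumption that the added people have a lower yield.

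The consequence is possible misclassification of adopters under the rule that all three rates must rise, and possible blunting or bias of the primary comparison. The direction and size of any effect on the between-arm result are not established. The figures above show only that count and share can diverge; they rest on assumed volumes and starting yields, and on survey figures for adults aged 18 or over. The number of compounds is unaffected.

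**What to change.** Use one definition of the detection component in both Study outcomes and the aim 2a analysis, and make it reflect detection volume: newly detected hypertensives over a fixed window, of the same length at baseline and at 12 months and identical in both arms. Two forms would serve:

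- **Per CHO.** This uses the numerator already to be collected and matches the CHO-level analysis.
- **Per 100 catchment adults.** This adjusts for zone size. Because about two CHOs share a zone and the CHO is the unit of analysis, it needs a stated rule for attributing zone detections and population to each CHO, for example dividing the zone population by its number of CHOs.

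Report the number screened beside the component, and keep the yield among those screened as descriptive only. Apply the same definition in the all-three-rates rule.

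The cost is wording in two sections and, for the second form, one adult population figure per zone. Catchment counts will be approximate, and the article does not show that they are already held, but they do not depend on whom a CHO chooses to measure. As enrolment has begun, the change should be dated and made before outcome data are examined by arm.

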### Objectives

The study has four specific objectives:
*Aim 1*: Identify practice capacity for the adoption of TASSH in CHPS zones and develop a culturally tailored PF strategy using qualitative methods.*Aim 2a*: Evaluate in a cluster randomized controlled trial (RCT) the effect of PF versus usual care (UC) on the adoption of TASSH across 70 CHPS zones at 12 months post-randomization.*Aim 2b*: Compare in a cluster RCT design the clinical effect of PF versus UC on systolic blood pressure (BP) reduction among 700 adults with uncontrolled HTN at 12 months post-randomization.*Aim 3*: Evaluate the sustainability of TASSH implementation across the CHPS zones at 24 months post-randomization (1 year after completion of the trial).*Aim 4*: Evaluate the mediators of the adoption of TASSH across the CHPS zones at 12 months post-randomization.

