#### Sample size and power estimates

The proposed design is a cluster randomized design to compare PF versus usual care. The primary outcome is a composite measure of adoption ratings to assess the degree to which the TASSH protocol is implemented at the CHPS compounds. The secondary outcomes are the difference in the change in systolic BP between patients at the CHPS sites randomized to PF versus those at the usual care CHPS sites. The unit of randomization is the CHPS compound, and the total sample size is the average number of CHOs at the CHPS sites who will provide the adoption ratings (primary outcome) at each site × the number of CHPS compounds and the average number of patients whose systolic BP will be assessed (secondary outcome) enrolled at each CHPS compound × the number of CHPS compounds. In order to estimate the number of CHPS compounds and the average number of CHOs and the average number of patients needed to have power of .80 for a hypothesis test with a type 1 error rate (alpha) of .05, we have assumed a moderate standardized effect size (*d*) of .50 of the difference in change in adoption ratings between the CHOs in the CHPS sites in the UC group versus those in the CHPS sites in the PF group from baseline to 12 months. We note that Baskerville et al. reported in a systematic review of practice facilitation in primary care settings an average effect size of *d* = .56 [15]. We also calculated the sample size for an assumed degree of dependency (intra-cluster correlation—ICC) of the CHOs’ data within CHPS compounds of .10. Thus, for an ICC of .10 and 2 CHOs providing the adoption ratings, our target number of CHPS compounds to recruit is 70. As such, a total of 140 CHOs will participate in this study. For the secondary outcome of patient change in systolic BP, we will have substantially greater power than .80 under the same effect size (*d* = .50) and ICC assumptions as we anticipate enrolling an average of 10 patients/compound. So, with 70 compounds, we would enroll 700 patients. Aim 3 concerns the correlation relationship between different mechanisms of change and the change in adoption ratings between baseline and 12 months. For this analysis, we will have the entire sample of 70 compounds and 140 nurses. With this sample and the same assumptions that we made for aim 2a and aim 2b, we will have power of .80 to detect a moderate correlation of .30. Finally, aim 4 concerns detecting a quadratic pattern consistent with sustainability across the baseline and 12- and 24-month time points. Again, the entire sample will be available for this analysis. The standardized effect size for the quadratic effect will depend considerably on the exact form of the quadratic pattern. The largest effect size would occur when the adoption is not sustained; that is when the adoption ratings revert to their baseline values after PF has ended. With the proposed sample size, we will have power greater than .90 to determine if this unwelcome event occurs.

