#### Analysis for aim 4: Inner setting variables (implementation climate, leadership support, organizational capacity) will mediate the effect of PF on adoption of TASSH at 12 months following randomization and sustainability at 24 months following randomization

In this analysis, we will evaluate the mediators of adoption and sustainability of the PF implemented TASSH program. In particular, we will assess the extent to which inner setting variables (e.g., implementation climate, leadership engagement, and organizational capacity) affect the degree of adoption of TASSH at 12 months utilizing structural equation modeling techniques. We will estimate a just-identified path model using the robust weighted least squares estimator to investigate relationships among the theoretical mediators of implementation climate, leadership engagement, and organizational capacity. Based on our conceptual model, we will test the direct effects from the theoretical constructs to adoption. In addition to the direct effects, the indirect effects from the PF intervention to adoption via inner setting variables will be estimated as the product of component direct effects and tested using bootstrapped 95% confidence intervals. As with previous models, random effects will be specified for CHPS and participant to account for the clustered nature of measurements.

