There are several potential methodological challenges that may be encountered during the project. First, it is likely that we will observe variations in the implementation of TASSH and the TSF strategy at CHPS zones randomized to the intervention condition. While we have defined the core elements of the TSF and the TASSH intervention, we acknowledge that adaptation to the unique practice context of CHPS zones will be necessary, particularly given the focus on community-based care. Prior studies suggest that this is an inherent component of practice facilitation with the goal to enhance adoption and sustainability. We will use fidelity checks to engage, enhance, and evaluate tasks of the CHOs so as to ensure that the core elements of the TSF strategy are implemented and documented to enhance external validity. Secondly, unforeseen changes in the outer settings of Ghana Health Systems and the CHPS zones may affect implementation outcomes (i.e., policy changes with HTN control, health insurance scheme). Semi-structured interviews every 6 months on CHO’s delivery of the intervention will be collected at each site to review and analyze for any threats to internal validity. Despite these limitations, the findings have potential for high impact by accelerating the tempo of implementation, adoption, and sustainability of evidence-based task-strengthening strategies for HTN control in sub-Saharan Africa. Findings will also provide policymakers and key stakeholders with the data they need to make decisions regarding dissemination and scale-up of effective task-strengthening strategies for HTN control.

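### As specified, Aim 4's 12-month indirect effect cannot tell mediation apart from adoption improving the mediator ratings; the mediator time points and earlier adoption need to be written into the analysis

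*Protocol article*

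**What the plan says.** Three places in the protocol article bear on when the mediators are measured.

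- **Objectives**, Aim 4: "Evaluate the mediators of the adoption of TASSH across the CHPS zones at 12 months post-randomization". Only 12 months is named.
- **Study outcomes**, secondary outcomes: mediators "of the adoption of TASSH across the CHPS zones at 12 and 24 months will be assessed".
- **Analysis for aim 4**, hypothesis: the inner-setting variables "will mediate the effect of PF on adoption of TASSH at 12 months following randomization and sustainability at 24 months following randomization".

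The model is fixed in the same analysis section: "We will estimate a just-identified path model using the robust weighted least squares estimator". Indirect effects from practice facilitation (PF) to adoption "will be estimated as the product of component direct effects and tested using bootstrapped 95% confidence intervals". No lag is stated, and no earlier mediator or adoption value enters the model.

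The power section describes the mechanism analysis as a "correlation relationship between different mechanisms of change and the change in adoption ratings between baseline and 12 months". The sections listing the mediator scales give no time points. The trial design section places an assessment of inner-setting variables in the pre-implementation phase, without naming the scales or giving them a role in the path model. Adoption is assessed from a questionnaire completed by the community health officers (CHOs).

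**The concern.** A mediation claim needs the mediator to change before the outcome does. If the ratings and adoption are taken together at 12 months, two explanations predict the same data: PF improves climate and leadership, which then raise adoption; or PF raises adoption, and CHOs who are using the programme rate their workplace more favourably. The second is plausible here. The scales record staff perceptions of support and reward for evidence-based practice, and the power section draws both sides of the mechanism analysis from the same 140 staff.

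The model cannot arbitrate. A just-identified path model has zero degrees of freedom, so no fit statistic can show that an arrow points the wrong way. Direction has to come from the order of measurement, and the text does not supply that order for 12 months. A significant indirect effect would be read as the mechanism by which PF works and could steer scale-up, which the Discussion names as a use of the findings.

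**Working it through.** **Inputs from the sample size section:** 70 compounds, 2 CHOs each, ICC .10, d = .50, power .80, alpha .05.

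**The plan's own figure reproduces.** Two-group comparison at d = .50: 63 CHOs per arm. Design effect 1 + (2 − 1) × .10 = 1.10. 63 × 1.10 = 69.3 per arm, so 35 compounds per arm and 70 in all. Power with 70 CHOs per arm is 0.805. The check below uses this same design.

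**Assumption.** The documents give no association between mediator and adoption, so the link c is varied from .1 to .7.

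**Reverse order only, true mediation zero, concurrent measurement.** Let X be the arm, Y adoption and M the rating:

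- Y = .5X + e, with unit variance and ICC .10
- M = cY + √(1 − c²)·u

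The fitted paths are then:

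- PF to mediator: a = .5c
- mediator to adoption given arm: b = cov(M,Y|X)/var(M|X) = c/1 = c
- indirect effect: ab = .5c²
- apparent share mediated: .5c²/.5 = c²

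For c = .3, .5 and .7 the apparent share is 9%, 25% and 49%, where the truth is 0.

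**How often the 95% interval for ab excludes zero:**

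| Link c | Cluster-robust errors, Monte Carlo interval (2,000 runs) | Cluster bootstrap (600 runs, 300 resamples) |
|---|---|---|
| 0 | not run | 0.5% |
| .1 | 1.5% | not run |
| .3 | 13% | 15% |
| .5 | 29% | 32% |
| .7 | 55% | 54% |

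**24-month sustainability with 12-month mediators.** Suppose 24-month adoption depends only on 12-month adoption, Y24 = ρ·Y12 + e, and the 12-month ratings again only reflect Y12. If Y12 is left out, M12 stands in for it: without baseline terms a = .5c, b = ρc and the total effect is .5ρ, so the apparent share is again c². Once Y12 is in the model, M12 carries nothing further and b = 0. Simulated frequency of a significant indirect effect, with the persistence of adoption ρ assumed at .5 to .7 for the baseline-only column:

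| Link c | Adjusted for baseline mediator and baseline adoption only | 12-month adoption in the model |
|---|---|---|
| .3 | about 4% | about 1% or less |
| .5 | 19–23% | about 1–2% |
| .7 | 53–61% | about 3% |

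Placing the mediator earlier is therefore not enough. Adoption at the time of the mediator measurement has to be a covariate.

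**The case against.** A reader might infer that the protocol fixes the mediators at the same times as adoption, so that the whole of Aim 4 fails. The documents do not support that.

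- **Timing is ambiguous.** In the secondary outcomes the time phrase can attach to adoption, as it does in the Objectives and in the Aim 4 hypothesis. The other reading is more natural, because the times in the neighbouring outcome items are assessment times, but it is not certain. If the times do belong to adoption, the visible text gives the mediator scales no follow-up time at all.
- **The schedule is not visible.** The flow chart and the SPIRIT figure are not shown, and an intermediate wave may be in them. That stands. It does not change the Aim 4 analysis section, which puts no such wave into the model.
- **There is an earlier assessment.** Inner-setting variables are assessed before implementation. A pre-randomization value helps with confounding, but it cannot carry a change caused by PF, so it does not order mediator and adoption at 12 months.
- **24 months differs.** If mediators are taken at 12 months, they precede 24-month adoption and a lagged analysis is possible. It is not specified.
- **Detail may be left to the analysis plan.** This would answer a missing model. Here the article already fixes identification, estimator, effect formula and interval, and attaches a directional claim to them.
- **The size is assumed.** Links of .3 to .7 and purely reverse causation are choices; at .1 the frequency is only 1.5%. The figures show what the design would let through, not what is likely in this trial.

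**Conclusion.** The concern holds for the 12-month indirect effect. As specified, it cannot distinguish PF acting through the mediators on adoption from PF raising adoption and adoption raising the ratings. Under the plan's own 70 × 2 design, with no true mediation and an assumed link of .3 to .7, about 13% to 55% of trials would show a significant indirect effect, with an apparent share mediated of about 9% to 50%.

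This rests on concurrent measurement, which is the most natural reading but not the only one, and on a continuous adoption score analysed with clustering-adjusted regression rather than the exact weighted least squares model. For 24 months the problem is one of specification: the data could support an ordered analysis if 12-month adoption is included.

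The randomized comparisons of adoption, systolic blood pressure and sustainability do not use the mediators and are unaffected. This is a change that should be made to a secondary aim; it does not threaten the trial.

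**What to change.** 1. **Time points.** In the secondary outcomes and in the Aim 4 analysis, state when each mediator scale is completed, separately from when adoption is assessed. At the same time reconcile the Objectives (12 months only) with the outcomes and analysis sections (12 and 24 months), and correct the power section, which swaps the labels of Aims 3 and 4.
2. **24-month sustainability.** Use the 12-month mediators, adjusted for the baseline mediator, baseline adoption and 12-month adoption. If the scales are taken at baseline and 12 months, this costs nothing beyond wording. The indirect effect then concerns adoption after month 12 given its level at month 12, and the text should say so.
3. **12-month adoption.** If a mediator wave between randomization and month 12 is already scheduled, use it with adoption measured at that same wave as a covariate. Otherwise report the result as an association, not mediation. This costs only the wording of the claim.
4. **Optional.** A new 6-month wave would be extra data collection: 32 + 12 + 18 = 62 items for 140 CHOs, plus adoption at that time. The Discussion plans site contacts at that interval ("Semi-structured interviews every 6 months on CHO’s delivery of the intervention will be collected at each site"), but these are interviews about delivery, so adding the scales would be new work.
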